##### 2.6.2.3 CAT

The CAT contains eight questions related to COPD symptoms, which patients answer according to their condition (35). In addition to assessing dyspnea, the test evaluates other COPD symptoms, including cough, sputum, and the ability to perform exercise.

##### 2.6.2.4 St George's Respiratory Questionnaire

The St George's Respiratory Questionnaire is the most widely documented comprehensive measure for assessing the quality of life in patients with COPD (36).

##### 2.6.2.5 Pulmonary function tests

Pulmonary function tests will be performed by professional assessors trained in spirometry (37). Participants will be asked to discontinue the use of bronchodilators before the test. Three measurements of the post-bronchodilator forced expiratory volume in 1 s and forced vital capacity will be recorded to diagnose COPD and assess the severity of airflow obstruction.

##### 2.6.2.6 6MWT

The 6MWT assesses exercise tolerance and laboratory-induced dyspnea. The test will be performed according to the guidelines issued by the American Thoracic Society in 2002 (38). After sitting at rest in a chair for at least 10 min, participants will walk back and forth to cover as much distance as possible for 6 min in a 30-m long flat and straight corridor. Rest will be allowed during the test; however, if the test ends early, the walking distance, time stopped, and the reason for stopping early will be recorded. If the test is stopped due to severe breathlessness, palpitations, or other signs of discomfort, the investigator will record the time and distance. The 6-min walk distance will be used as the outcome measure. Before and after the test, heart rate, oxygen saturation, Borg Dyspnea Scale score, and VAS score will be measured. Monitoring the heart rate will enable the assessment of exercise intensity.

##### 2.6.2.7 Hospital Anxiety and Depression Scale

The Hospital Anxiety and Depression Scale is a patient-reported score based on a 14-item questionnaire to assess the severity of anxiety and depressive symptoms and is an effective and reliable method of screening for identifying emotional disorders during hospitalization (39). Participants select the answers that best reflect their current emotional state.

### 2.7 MRI

Participants will undergo MRI four times, performed using a 3.0 T superconductor (Magnetom Skyra; Siemens Healthineers, Erlangen, Germany). At baseline, resting-state MRI will be performed after symptom assessment, and post-exercise MRI will be performed immediately after the 6MWT to capture images during dyspnea. After the intervention period, resting-state and post-exercise MRI will be repeated. While undergoing an MRI scan, the participants will be required to maintain head and neck stability and keep their eyes open. A whole-brain anatomical image consisting of 192 sagittal slices with a thickness of 1 mm will be collected using a T1-weighted 3D sequence with the following parameters: repetition time = 2,300 ms, echo time = 2.26 ms, flip angle = 8°, voxel size = 1 × 1 × 1 mm, and inversion time = 900 ms. Functional MRI will be performed using an echo-planar imaging sequence with the following parameters: repetition time = 2,000 ms, echo time = 30 ms, flip angle = 70°, voxel size = 2 × 2 × 2.5 mm, and number of slices = 54. In addition, diffusion tensor imaging will be performed using the following parameters: repetition time = 5,100 ms, echo time = 80 ms, and voxel size = 1.7 × 1.7 × 2 mm.

Two experienced radiologists will review all images to identify abnormalities including brain damage, structural brain lesions, and artifacts.

### 2.8 Statistical analysis

Qualitative variables will be expressed as numbers (percentages), and quantitative variables will be expressed as mean (standard deviation) or median (interquartile range [25%−75%], q1–q3). All efficacy evaluation data will be summarized according to the full analysis set and the per-protocol set. For safety analysis, the safety set will include all randomized participants who received at least one interventional treatment. A paired *t*-test or Wilcoxon signed-rank test will be conducted to compare the outcomes at baseline with those after the 8-week intervention period and during follow-up within a group. Analysis of covariance will be performed to compare the results after acupuncture and during follow-up between the groups. Exercise intensity will be adjusted to assess post-exercise dyspnea. Data will be analyzed using SPSS software version 26.0 (IBM Corporation, Armonk, NY, USA), and statistical significance will be set as a *p*-value of < 0.05.

Metadata from DICOM files will be converted to BIDS using HeuDiConv. fMRIPrep software version 21.0.4, a combination of tools from common software packages including FSL, ANTs, FreeSurfer, and AFNI, was developed by the laboratory of Russ Poldrack and the Stanford Center for Reproducible Neuroscience and will be used to perform minimal data preprocessing, including skull stripping, motion correction, segmentation, co-registration, and normalization. Motion artifacts will be removed automatically using independent component analysis (40). Subsequently, graph theory-based or data-driven approaches will be used to compare the differences between the DAM and NAM groups.

PANDA, a MATLAB toolbox that can be downloaded from https://www.nitrc.org/projects/panda/ and is based on MATLAB R2016a in the Ubuntu 16.04 operating system, will be used to analyze brain diffusion images. The coupling value between the functional connection matrix and the structural joint matrix will be calculated and correlated with clinical symptoms.

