### 2.4 Sample size

The sample size calculation was based on the dyspnea visual analog scale (VAS) score, as reported by Liu et al. (29). The test for paired means in PASS software version 15.0.5 (NCSS Statistical Software, Kaysville, UT, USA) was used to calculate the dyspnea VAS score differences in the placebo and acupuncture groups before and after acupuncture, which determined that a total of 78 patients with stable COPD should be included in the study to achieve a statistical power of 0.95 and a significance level of 5% for difference detection. Assuming a dropout rate of 15% established the necessity of a sample size of 45 participants per group. The sample size calculation based on the Borg Dyspnea Scale, as reported by Li et al. (30), showed that a total of 16 patients with stable COPD should be included in the study to achieve a statistical power of 0.97 and a significance level of 5% for difference detection. Assuming a dropout rate of 20%, a sample size of 10 participants per group is required. This study, being a multicenter, clinical, randomized controlled trial, requires a larger sample size. Therefore, a sample size of 90 participants is considered to be reasonable for this study.

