### 2.5 Intervention

Participants will be randomly categorized into two parallel groups to undergo acupuncture at acupoints on the DAM or non-acupoints on the NAM for 8 weeks (every 2^nd^ day, three times a week). The six standardized acupoints on the DAM are as follows: (1) EX-B1 (Dingchuan), (2) BL13 (Feishu), (3) BL20 (Pishu), (4) BL23 (Shenshu), (5) LU7 (Lieque), and (6) ST36 (Zusanli) (Table 2). The six non-acupoints on the NAM have been designed to be 2.0 cun away from the acupoints on the DAM listed above (Figure 3). Acupuncture will be performed on patients in the prone position, using disposable stainless-steel needles inserted into the disinfected skin. The locations, directions, and depths of needle insertion are presented in Table 2. Minor stimulation, achieved by lifting and thrusting the needles along with thrusting and rotating the needle sheath, will be applied to produce the sensation known as deqi (a feeling of soreness, numbness, distention, or radiation, which is considered effective). Acupuncture needles will be inserted at the intended acupoints for 30 min.

**Table 2 T2:** Location of acupoints on the disease-affected meridian.

**Acupoints**	**Location**	**Depth**	**Direction**
Dingchuan (EX-B1)	On the back of the neck, 0.5 cun apart from the midpoint of the lower edge of the spinous process of the seventh cervical vertebra	0.5–1.0 cun	Vertically puncture or the needle point toward the spine
Feishu (BL13)	On the back, 1.5 cun apart from the spinous process of the third thoracic vertebra	0.5–0.8 cun	Oblique puncture
Pishu (BL20)	On the back, 1.5 cun apart from the spinous process of the eleventh thoracic vertebra	0.5–0.8 cun	Oblique puncture
Shenshu (BL23)	1.5 cun apart from the spinous process of the second lumbar vertebra	0.5–1.0 cun	Vertically puncture
Lieque (LU7)	On the radial side of the forearm and above the radial styloid process, between the brachioradialis muscle and the abductor pollicis longus tendon, 1.5 cun above wrist crease	0.2–0.3 cun	Upward oblique puncture
Zusanli (ST36)	On the outside of the shank, 3 cun below Dubi^*^ and a thumb lateral to the anterior tibial ridge	1.0–2.0 cun	Vertically puncture

^*^Dubi (ST35): when the knee is bent at a right angle, the acupoint is located at the concave position on the outer side of the patellar ligament of the knee joint.

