To the best of our knowledge, this study is the first to investigate the neurobiological mechanisms of acupuncture for the treatment of dyspnea in patients with COPD. Importantly, non-acupoints on the NAM have been included as a placebo control. In this study, various dyspnea assessment scales were used before and after exercise and acupuncture. Additionally, diffusion tensor imaging and functional MRI data were collected to investigate the mechanisms of exertional dyspnea and its emotional impact on patients with stable COPD. Since dyspnea is a complex experience that can be caused or influenced by many factors and dimensions, we evaluated the effects of acupuncture on dyspnea from multiple aspects, including emotions and quality of life.

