## 4 Conclusion

This article introduces the design and scheme of a clinical trial to study the effects and neurobiological mechanisms of acupuncture treatment of dyspnea in patients with COPD. The results of this innovative research are expected to answer the following questions: As an alternative therapy, can acupuncture effectively alleviate dyspnea in COPD? How can functional and structural imaging explain the occurrence of exertional dyspnea in COPD? Does acupuncture relieve dyspnea by regulating the respiratory-related areas of the brain? Does acupuncture relieve dyspnea by regulating areas related to emotions? The results of this trial will provide novel insights into the mechanisms of dyspnea and provide evidence and principles for the use of acupuncture to alleviate dyspnea in COPD and other diseases involving dyspnea.

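### Within-group before-after tests stand beside the between-group ANCOVA with neither named decisive, and the stated 0.95 power belongs to a paired test, not to the randomised comparison

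*Protocol article*

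**What the plan says.** **Analysis (section 2.8).** Two kinds of test are planned. Within each arm there are paired t-tests, with a rank-based alternative: "Wilcoxon signed-rank test will be conducted to compare the outcomes at baseline with those after the 8-week intervention period and during follow-up within a group". Between arms, "Analysis of covariance will be performed to compare the results after acupuncture and during follow-up between the groups". One significance threshold, p below 0.05, covers both. Neither kind of test is named as the one that decides efficacy.

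**Sample size (section 2.4).** The method is given as "The test for paired means in PASS software version 15.0.5", and the article says that this "was used to calculate the dyspnea VAS score differences in the placebo and acupuncture groups before and after acupuncture". The result is 78 patients in total at power 0.95 and a 5% significance level, raised to 45 per group for 15% dropout. No mean difference, SD, correlation or sidedness is given.

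**Comparator.** Section 2.5 introduces both arms and then describes one needling procedure. It includes stimulation to produce deqi, glossed as "a feeling of soreness, numbness, distention, or radiation, which is considered effective". The section does not limit this to the DAM arm and gives no separate technique for NAM. Its closing sentence and Table 2, however, mention only acupoints. Section 3 states that "non-acupoints on the NAM have been included as a placebo control", and section 2.4 also calls the control group placebo.

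**Target claim.** Hypothesis (1) in section 1 is that acupuncture is an effective treatment for COPD. Section 4 asks: "can acupuncture effectively alleviate dyspnea in COPD"?

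**The concern.** A significant before-after change in one arm is not evidence of a treatment effect. Patients may improve through natural course, regression to the mean, expectation or practice at the walking test, and a paired test counts all of it. Randomisation exists to remove these components, and a within-arm test does not use it.

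The paired tests are hard to treat as a harmless descriptive extra. They carry the same p < 0.05 threshold as the ANCOVA, and the stated power of 0.95 was computed for a paired test. With no ranking of the tests, the trial could report a significant improvement in DAM, or significance in DAM but not in NAM, as a finding of efficacy while the randomised comparison shows nothing. A reader may also take 0.95 to be the power of the DAM-versus-NAM comparison.

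A second, smaller matter affects what the ANCOVA result means. If both arms are needled, the comparison concerns needling at one set of points against another, while the hypothesis and conclusion are worded for acupuncture as such.

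**Working it through.** **Inputs.** From section 2.4: 78 evaluable in total, power 0.95, significance level 5%. Allocation is 1:1 (section 2.3), so 78 / 2 = 39 per arm. Effect sizes are not stated. All those below are assumptions, in units of the SD of the before-after change. Tests are taken as two-sided.

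**Step 1. Can the 78 be reproduced?** No, because the effect size and SD are missing. The effect it implies can be solved for. For a paired test on n pairs with standardised change d, power = P(T > t₀.₉₇₅,ₙ₋₁), where T is noncentral t with n − 1 degrees of freedom and noncentrality d√n.
- If 78 means 39 pairs in each arm: d = 0.592 (0.592 × √39 = 3.70, critical value 2.024) gives 0.95.
- If 78 means 78 pairs: d = 0.413 (0.413 × √78 = 3.65, critical value 1.991) gives 0.95.

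The text does not settle which is meant, so both are carried forward.

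**Step 2. Within-group tests when the arms do not differ.** Let both arms improve by the same d, with 39 per arm. Let p be the probability that the DAM paired test is significant for improvement. The arms are independent, so the probability of significance in DAM but not in NAM is p(1 − p).

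| Shared improvement d (SD of change) | p: DAM paired test significant | p(1 − p): DAM only |
|---|---|---|
| 0.2 | 0.229 | 0.177 |
| 0.3 | 0.447 | 0.247 |
| 0.4 | 0.682 | 0.217 |
| 0.413 | 0.710 | 0.206 |
| 0.5 | 0.861 | 0.120 |
| 0.592 | 0.950 | 0.048 |

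In every row the true between-arm difference is zero. A two-sided 5% between-group test would favour DAM 2.5% of the time. The 0.95 in the last row is true by construction, since 0.592 was solved for to give it. The informative part is the whole range.

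**Step 3. Power of the randomised comparison.** For a two-sample test with 39 per arm, unadjusted for baseline, the noncentrality is d√(39/2) on 76 degrees of freedom, critical value 1.992.
- True difference 0.592 SD: 0.592 × √19.5 = 2.61, power 73%.
- True difference 0.413 SD: 0.413 × √19.5 = 1.82, power 44%.
- Detectable difference: 0.83 SD at 95% power, 0.64 SD at 80% power.

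Baseline adjustment in the ANCOVA would raise these powers somewhat. By how much cannot be computed, because no correlation is stated.

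**Step 4. If NAM needling has some effect.** Assume a DAM effect of 0.83 SD. Between-group power is about 95%, 77%, 44% or 15% when NAM keeps 0%, 25%, 50% or 75% of that effect. An active control therefore makes the test conservative. It does not raise its false-positive rate.

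**The case against.** The strongest reply is that the plan does contain the right test. The ANCOVA is announced in the sentence after the paired tests, and it is a valid randomised comparison. Nothing in section 2.8 calls the paired tests primary, and nothing says that efficacy will be claimed from DAM alone. A full protocol or analysis plan may rank the tests.

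Much of this stands. A reader might infer that neither planned test can support any claim about acupuncture. The document does not support that. A DAM advantage on the ANCOVA would be evidence for needling at those acupoints, and an active control would make that evidence harder to obtain, not invalid. A reader might also infer that the NAM arm certainly receives deqi stimulation. That is the natural reading of section 2.5, but it is not stated, since Table 2 and the closing sentence speak only of acupoints.

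Two things remain. The point does not rest on a missing detail. The article itself states within-group significance tests at the common threshold, and itself attaches its power to a paired test. The effect sizes in the working are assumptions, and the 95% figure at 0.592 SD is circular if read alone. Even so, the paired test misleads across the whole range shown.

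**Conclusion.** The concern holds in this limited form. The plan places within-group significance tests beside the ANCOVA without making the ANCOVA decisive, and its 0.95 power is that of a paired test.

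With no between-arm difference, the DAM paired test would be significant about 23% to 95% of the time, and significance in DAM alone would occur about 5% to 25% of the time, for shared improvements of 0.2 to 0.592 SD. If the true between-arm difference equalled the implied paired effect, the unadjusted between-group power would be about 73% (0.592 SD) or 44% (0.413 SD), not 95%. These figures assume 39 evaluable per arm, two-sided 5% tests and effect sizes that the protocol does not give.

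The ANCOVA validly tests needling at DAM acupoints against needling at NAM non-acupoints. It cannot estimate acupuncture against no needling. If it is null, it cannot separate no effect from an effect in both arms. Sections 2.5 and 3 need to be reconciled on what the control receives.

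**What to change.** 1. In section 2.8, state that efficacy claims rest only on the randomised DAM-minus-NAM ANCOVA: at week 8 for the primary outcome, and likewise between groups for the follow-up outcomes.
2. Report within-group changes as means with confidence intervals, without p-values or efficacy wording.
3. In section 2.4, state that the 0.95 power refers to the paired test. Add the power of the between-group comparison at 39 per arm, with the assumed difference and SD. N need not change.
4. Word hypothesis (1) and the efficacy conclusion as needling at DAM acupoints versus needling at NAM non-acupoints.
5. Reconcile section 2.5 with the placebo label in section 3 by stating whether the deqi procedure described there applies to the NAM arm.

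The cost is text and one power calculation, with no change to conduct or data collection. The downside is a narrower headline claim and a less favourable stated power.

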**Methods:**

This is a prospective, multicenter, single-blind, randomized controlled trial. A total of 90 participants will be recruited from three centers and will be randomly assigned in a 1:1 ratio to undergo acupuncture at acupoints on the disease-affected meridian (DAM) or non-acupoints on the non-affected meridian (NAM), in addition to routine pharmacological treatments. All participants will undergo 30 min of acupuncture three times a week for 8 weeks and will be followed up for 12 months. The primary outcome will be the severity of dyspnea, as measured using the Borg Dyspnea Scale and a visual analog scale at rest and after exercise. The secondary outcomes will include the multidimensional profile of dyspnea using Dyspnea-12, the modified Medical Research Council Dyspnea Scale, and the COPD assessment test; quality of life assessments using St George's Respiratory Questionnaire and the Hospital Anxiety and Depression Scale; and additional measurements of exacerbation frequency, pulmonary function, and the 6-min walking distance. Magnetic resonance imaging (MRI) will be performed before and after exercise to explore the potential neurobiological mechanisms of exertional dyspnea. Anxiety and depression will be measured and analyzed for their correlation with the activation of specific brain areas involved in dyspnea.

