## 2 Methods and analysis

### 2.1 Study design

This is a prospective, multicenter, randomized, single-blind trial with two parallel groups involving patients with stable COPD. As shown in Figure 2, sociodemographic data will be collected, and participants will complete symptom questionnaires and undergo magnetic resonance imaging (MRI) before and after the 8-week intervention period. Patients will be followed up for 12 months via telephone interviews to perform COPD assessment test (CAT) and record COPD exacerbations. The exact timing of each outcome measurement is presented in Table 1.

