**Figure 2 F2:**
[figure not shown]
Study flowchart.

**Table 1 T1:** Study schedule.

**Measurements**	**Screening visit**	**Visit 1 baseline**	**Visit 2 8 weeks**	**Phone interview 6 months**	**Phone interview 9 months**	**Phone interview 12 months**
Demographics, smoking history, and medical and treatment history	×	×				
Spirometry		×	×			
Dyspnea (Borg dyspnea scale and VAS)		×	×			
Dyspnea-12		×	×			
mMRC	×	×	×			
CAT		×	×	×	×	×
SGRQ		×	×			
6MWT		×	×			
Exacerbation		×	×	×	×	×
HADS		×	×			
MRI		×	×			

VAS, visual analog scale; mMRC, Modified Medical Research Council Dyspnea Scale; CAT, chronic obstructive pulmonary disease (COPD) assessment test; SGRQ, St George's Respiratory Questionnaire; 6MWT, 6-min walking test; HADS, Hospital Anxiety and Depression Scale; MRI, magnetic resonance imaging.

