#### 2.2.2 Inclusion criteria

The inclusion criteria are as follows: (1) diagnosis of COPD with clinically stable symptoms and no antibiotic or corticosteroid use, emergency room visits, or any hospitalizations due to COPD exacerbation in the preceding 4 weeks; (2) moderate-to-very severe airflow obstruction, defined as the post-bronchodilator forced expiratory volume in 1 s being < 80% predicted; (3) aged 40–80 years without limitation of sex; (4) ability to walk unaided; (5) no pulmonary rehabilitation in the preceding 6 months; and (6) willing to cooperate with the study and provide written informed consent.

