#### 2.2.4 Withdrawal criteria

During the intervention period, enrolled participants will be withdrawn from the study if they (1) experience serious adverse reactions or unexpected events that prevent continuing participation; (2) experience serious complications or a deterioration in their condition requiring urgent treatment; (3) express a request to withdraw from the clinical trial; or (4) express the intent that do not want to complete the planned treatment.

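### The generic within-group before/after test in section 2.8 reaches exacerbation counts, where it would measure window length and entry selection rather than treatment

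*Protocol article*

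**What the plan says.** The abstract lists among the secondary outcomes "additional measurements of exacerbation frequency, pulmonary function, and the 6-min walking distance". Section 2.1 states: "Patients will be followed up for 12 months via telephone interviews to perform COPD assessment test (CAT) and record COPD exacerbations". The exacerbation row of Table 1 is marked at baseline, at Visit 2 (8 weeks) and at three telephone contacts, the first labelled "Phone interview 6 months" and the others at 9 and 12 months. The only other row marked at the telephone contacts is CAT.

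Section 2.8 sets two tests. Within each group, a paired t-test or Wilcoxon signed-rank test is to "compare the outcomes at baseline with those after the 8-week intervention period and during follow-up within a group". Between groups, it says: "Analysis of covariance will be performed to compare the results after acupuncture and during follow-up between the groups". No outcome is exempted, and exacerbations are not named.

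Three other places bear on the point. Inclusion criterion 1 (section 2.2.2) requires "no antibiotic or corticosteroid use, emergency room visits, or any hospitalizations due to COPD exacerbation in the preceding 4 weeks". Section 2.2.4 withdraws participants who "experience serious complications or a deterioration in their condition requiring urgent treatment". Section 2.4 states: "Assuming a dropout rate of 15% established the necessity of a sample size of 45 participants per group".

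**The concern.** CAT is a score taken at one moment, so comparing a later value with baseline makes sense. An exacerbation count depends on how long the patient was watched. The article gives no look-back length for the baseline entry, and the later intervals differ from one another. A before/after test on such counts can be significant with no change in the underlying rate. Depending on the look-back, it could report a striking reduction or a worsening, in both arms.

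The entry rule adds a second distortion: the last four weeks before enrolment are selected to be free of treated exacerbation. What is at stake is an unsupported statement that exacerbations fell (or rose) after acupuncture, in one of the only two outcomes followed to 12 months.

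**Working it through.** **Does the rule reach exacerbations?** Both sentences in section 2.8 extend to follow-up. Table 1 shows only CAT and exacerbations recorded then. So the rule covers exacerbations by default.

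**Inputs.** From the documents: contacts at baseline, 8 weeks, 6, 9 and 12 months; four exacerbation-free weeks before entry; 45 per arm, or 39 per arm (78/2) before the dropout allowance; 15% dropout. The documents give no exacerbation rate, event count or power, so there is no stated figure to reproduce. Assumed: 0.5 to 1.5 exacerbations per patient-year, and gamma variation between patients with variance 0.7.

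**Windows.** If months run from baseline: 8 weeks; 26 − 8 = 18 weeks; 13 weeks; 13 weeks. If they run from the end of treatment, the second interval is 26 weeks. They are unequal either way.

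**Expected counts with nothing changing** (rate × weeks/52, rate 1.0): 0.15 in 8 weeks, 0.35 in 18 weeks, 0.25 in each 13-week interval, 1.00 in 12 months.

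**Apparent change at week 8, by look-back:**
- 12 months: 1 − 8/52 = 0.85, an 85% fall at any rate. If the entry rule empties the last four weeks, 1 − 8/48 = 0.83.
- 4 weeks: the baseline is about zero for treated events by eligibility, so any later event looks like worsening.

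**Within-group false positives** (constant rate, no effect, paired t-test in 39 patients, two-sided 5%, 1,500 runs; entry selection not modelled):

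| Baseline vs later window (weeks) | 0.5/yr | 1.0/yr | 1.5/yr |
|---|---|---|---|
| 52 vs 8 | 94.9% | 99.9% | 100% |
| 52 vs 44 | 6.1% | 9.6% | 12.6% |
| 4 vs 8 | 7.8% | 14.5% | 18.9% |
| 52 vs 52 | 5.0% | 4.3% | 4.7% |
| 8 vs 8 | 3.7% | 3.3% | 4.9% |

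Equal windows bring the error to 5% or below, so window length is the cause. The Wilcoxon test was not simulated.

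**Between-group ANCOVA** (follow-up count on arm and baseline count). In the same scenarios, with 39 per arm and complete follow-up, type I error was 3.5–5.1% and the mean estimate about zero, even where baseline and follow-up windows differed. With 45 per arm, 12-month windows and leaving times uniform over the year:

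| Dropout by arm | Type I error (0.5, 1.0, 1.5/yr) | Mean bias (events) |
|---|---|---|
| 15% / 15% | 4.8%, 5.1%, 5.2% | about 0 |
| 10% / 20% | 4.5%, 5.1%, 5.5% | −0.02, −0.06, −0.06 |
| 5% / 25% | 6.7%, 7.7%, 7.9% | −0.05, −0.10, −0.14 |
| 0% / 30% | 7.5%, 9.1%, 10.9% | −0.09, −0.15, −0.22 |

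The bias follows from lost time. For 5%/25%, mean exposure is 1 − 0.05 × 0.5 = 0.975 years against 1 − 0.25 × 0.5 = 0.875 years, a difference of −0.10 years times the rate. Simulation error near 5% is √(0.05 × 0.95/1,500) = 0.6 percentage points, so 10%/20% cannot be told from nominal.

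**The case against.** The strongest reply is that section 2.8 is a condensed general rule. It names no exacerbation analysis, section 2.6.2 has no subsection on exacerbations, and the full protocol or SAP may define the look-back, a rate or a count model. The word frequency may already mean a rate. This stands in part. On a rate scale the 85% artefact disappears and the null change is zero for every pair of windows. What remains is the entry selection: with a 12-month look-back the baseline rate would be understated by 4/52, about 8%, and with a 4-week look-back almost wholly. The absence of a count model is not the finding. The finding is that the stated before/after rule, which expressly extends to follow-up, covers an outcome it does not suit.

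It is also fair that the before/after tests are descriptive beside the randomised contrast, and that the size of the error turns on an unstated look-back: 52 against 44 weeks gives only 6–13% false positives.

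A reader might infer that the unequal windows also bias the comparison between arms, or that ANCOVA must give wrong intervals for counts. Neither is supported. Both arms follow one schedule, and type I error stayed near nominal unless observed time differed strongly by arm. The withdrawal rule makes such a difference possible, since observation can end because of deterioration, but nothing in the documents builds in an imbalance between arms. Nor is a count model clearly better calibrated here: in a separate null simulation (45 per arm, rate 1, dispersion 1, 1,000 runs) negative binomial Wald tests rejected in 5.5–7.3% of runs against 5.2–7.7% for ANCOVA, and 2–5% of fits failed.

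**Conclusion.** The point holds for the within-group test and only conditionally for the between-group test. If raw counts are used, the before/after test on exacerbations measures window length and selection. The 85% apparent fall does not depend on the event rate, but it does assume a 12-month look-back; the false-positive rates also rest on the assumed rates and dispersion. ANCOVA ignores person-time, which matters only if follow-up differs materially by arm: about 7–8% type I error at 5% versus 25% dropout, and near nominal at 10% versus 20%. Those dropout splits are illustrations; the article assumes 15% without a split by arm. This is a minor point on a secondary outcome. It does not touch the primary analysis or the sample size.

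**What to change.** - Exclude exacerbations from the within-group before/after tests.
- Define the baseline look-back and the follow-up window, including whether months run from baseline or from the end of treatment.
- Compare arms from randomisation to 12 months by negative binomial regression, or Poisson regression with robust errors, with a log person-time offset. Report the rate ratio with 95% CI and rates per patient-year.
- Adjust for the baseline exacerbation count once its look-back is defined. Table 1 lists medical history and a baseline exacerbation entry but no prior-year count, so the recall question has to be specified rather than assumed to exist.

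The cost is analysis wording and one defined question at baseline; visits and sample size do not change. There are two small downsides. A minority of negative binomial fits may not converge at 45 per arm, so a fallback (for example the robust Poisson model) should be named in advance. And the offset corrects unequal exposure but not withdrawal that depends on the patient's exacerbations, so person-time and reasons for leaving should be reported by arm.
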